### Participants and setting

This study will include a sample of the general Australian community as well as six subgroup population groups. Trial 1 will only include participants from the six vulnerable population groups, Trial 2 will only include participants from the general Australian community, and Trial 3 will include participants from all six vulnerable subgroups as well as the general Australian community.

These communities can be argued to be vulnerable to infection, transmission and experiencing negative health and other outcomes during the COVID-19 pandemic on the basis of their pre-existing lower health equity due to socioeconomic factors, increased risk of COVID-19 exposure, cultural factors, need for support for decision making due to intellectual or cognitive changes and/or augmentative or alternative communication methods or challenges experienced in communicating (Table 1) [10, 39, 40].

**Table 1 pone.0280865.t001:** Project population subgroups and their associated COVID-19 risk factors & communication challenges.

COVID-19 risk factors & communication challenges	Population subgroup					
	Aboriginal & Torres Strait Islander peoples	People living with disability & their carers	Refugee & asylum seekers	Deaf, hard of hearing people	Aged care workers	Street-based sex workers
Higher exposure risk		**Applicable** [12, 41] due to personal care tasks			**Applicable** due to work	**Applicable** [6, 7] due to work
Higher rates of health conditions & need for health services	**Applicable** [12, 41]	**Applicable** [12, 41]	**Applicable** [42]			**Applicable** [7]
Difficulty accessing health care	**Applicable** [41]		**Applicable** [42]			**Applicable** [6, 7]
Higher rates of limited English proficiency			**Applicable**		**Applicable**	
Lower rates of digital literacy and access to the Internet or Internet-enabled devices		**Applicable** [43, 44]				
Limited accessible COVID-19 information		**Applicable** [12]		**Applicable** [45]		
Loss of educational support and access		**Applicable**	**Applicable**	**Applicable** [46]		
Different cultural understandings of illness	**Applicable**		**Applicable**			
Lower SES	**Applicable** [47]	**Applicable** [12]	**Applicable** [42]			**Applicable** [7]
Higher rates of contract, casual or precarious work		**Applicable** [48]			**Applicable**	**Applicable** [6, 7]
Housing situation	**Applicable** [47] Larger, multi-family households		**Applicable** Larger, multi-family households			**Applicable** [6] Lack of appropriate housing

Participant groups in this study will be:

People who are currently living with a disability or a carer of someone who has a disability.Aged care workers.Refugee and asylum seekers with limited English proficiency whose first language is either Dari or Sinhalese. We limited this group to two non-English speaking communities as a project feasibility measure. None of the people in this cohort have Australian citizenship.Deaf and hard of hearing people who are Auslan users.Aboriginal and Torres Strait Islander peoples.Street-based sex workers.General Australian community.

People not currently living in Australia or who are under the age of 18 years will be excluded from this research.

Participants across all trials will observe the videos either in their own home (due to the online nature of the surveys), or at a partner organisation service provider location relative to their vulnerable population subgroup (if applicable). For example, participants in the Aboriginal Torres Strait Islander subgroup, may complete the survey at a common community meeting place.

### Interventions

#### Trial 1 (vulnerable groups only)

This trial will involve factorial allocation of two intervention factors each with two levels (2x2 factorial) across four context areas. These factors are:

Factor 1: Who is providing the message (general practitioner versus community representative).Factor 2: How is the message being delivered (animation versus talking head).

Both general practitioners and community representatives will be selected due to their high level of perceived trust in vulnerable subgroup communities, making them a viable potential deliverer of messages in real life. However, from a public health messaging perspective, a general practitioner can be used to develop a message that may potentially impact a range of vulnerable groups quickly in a pandemic context, whereas it takes more time and greater cost to produce messages delivered by specific vulnerable community representatives as each vulnerable community requires its own representative and own message to be produced. The talking head versus animation intervention approaches were selected as both are commonly used, yet are competing visual imagery approaches in public health messaging.

The project team contains a general practitioner who will perform this role for materials production. Scripting of the intervention messaging will be consistent with publicly available messages that have been forwarded by government and will be held as constant as feasible between the intervention levels. Community representatives will be specifically selected for each subgroup population based on their established leadership. They will also be invited to co-design messaging to ensure it is appropriate for the specific vulnerable population. Two of the vulnerable subgroup populations will require translation (of the written survey material) and interpreting (of the video content). This will be English to Dari and Sinhalese translation and interpretation for refugee and asylum seeker subgroup who have limited English proficiency and English to Auslan interpreting for the deaf and hard of hearing subgroup. During the video production phase, we will aim to ensure the consistency of ‘who’ across the general practitioner and community representative videos by purposely using a community representative who is recognisable and familiar to the participants. For these groups, interpretation of the general practitioner videos will be completed by a different person (who will not be as recognisable or familiar to the participants). For the refugee and asylum seeker subgroup, the general practitioner interpreter will not be visible on screen and provide spoken interpretation only, into either Dari or Sinhalese (English subtitles will remain on screen for both community representative and general practitioner videos). For the deaf and hard of hearing subgroup, the interpreter will remain on screen providing Auslan interpretation, with English subtitles also available for all videos except the community representative videos.

These contexts across which the intervention levels will be provided will be:

Having a booster vaccineWearing a mask outdoors when you can’t physically distanceStaying at home when you have a new cough symptomUsing QR check in codes when required

Video-based public health messages will be constructed to be up to 2 minutes in duration which we considered to be the upper limit of time used for public health messaging.

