### Procedure

Vulnerable subgroup populations will be recruited from partner organisations listed in Table 2. An advertisement via email, in person or via the partner organisation social media pages will be used, explaining the basic details of the project and what is required. A link to the explanatory statement and survey will also be included in this advertisement and participants will be able to complete the survey independently in their own time, with assistance from a family member or carer, or with assistance from a member of the corresponding partner organisation team if completing the survey on site. All information (explanatory statements, survey questions and video information) will be captioned, translated, interpreted or adapted accordingly to the communication profiles of the different vulnerable subgroup populations. This includes Auslan for the deaf and hard of hearing group, and Dari and Sinhalese for the refugee and asylum-seeker group. The general community group will be recruited online using social media platforms (i.e. Facebook and Twitter).

**Table 2 pone.0280865.t002:** Partner organisations related to each subgroup population.

Vulnerable Subgroup	Partner Organisation
**People living with a disability and their carers**	Able Australia, Wallara and Yooralla
**Aged care workers**	Donwood Community Aged Care Services
**Refugee and asylum seekers**	enliven
**Deaf, hard of hearing people**	Expression Australia and Able Australia
**Aboriginal and Torres Strait Islander peoples**	Peninsula Health
**Street-based sex workers**	St Kilda Gatehouse
**General Australian community**	Not applicable.

Randomisation will occur automatically via the inbuilt randomisation function on the Qualtrics data collection platform (Qualtrics, Provo, UT, USA). Therefore, random allocation will be fully concealed from participants and investigators involved in recruitment and data collection.

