### Analysis

The comparisons we will undertake across the three trials will be:

#### Trial 1

Main effect of who is providing the message (General Practitioner versus community representative).Main effect of visual stimulus (talking head versus animation).Interaction effect between these two main effects.Simple effects if interaction effect is significant.

#### Trial 2

General practitioner talking head visual stimulus delivered health message versus animated general practitioner visual stimulus delivered health message.Politician visual stimulus delivered health message versus general practitioner talking head visual stimulus delivered health message.Written delivery of health message (control) versus all other intervention types (general practitioner talking head, general practitioner animation and politician delivered health message).

#### Trial 3

The effectiveness of health information provision delivered through a conversational training approach by a general practitioner versus through a direct information provision approach by a general practitioner.

Comparisons will not be made between context areas as part of the primary analysis. However, we will investigate interaction effects of the different intervention comparisons across the different context areas and population subgroups so that we can understand whether certain interventions work better in certain contexts and populations.

Linear mixed model analyses will be used treating the intervention levels as fixed factors and participants as random factors. Context will be ignored when investigating intervention main effects as it will be balanced across the different intervention levels.

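### In the deaf and hard of hearing subgroup of Trial 1, English subtitles accompany the GP videos but not the community-representative videos, so subtitle availability cannot be separated from 'who' there

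*Protocol article*

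**What the plan says.** The protocol article (Interventions, Trial 1) sets up a 2x2 factorial across four context areas. Factor 1 is the messenger (GP or community representative) and Factor 2 is the visual format (animation or talking head).

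The same section describes the two subgroups that need interpreting, and it treats subtitles differently in each:

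- Refugee and asylum seeker subgroup: "English subtitles will remain on screen for both community representative and general practitioner videos".
- Deaf and hard of hearing subgroup: an Auslan interpreter on screen, "with English subtitles also available for all videos except the community representative videos".

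Participants and setting defines the second subgroup as "Deaf and hard of hearing people who are Auslan users". The Trial 1 section adds that, in both interpreted subgroups, the GP videos are interpreted by someone other than the community representative, and that this person is less familiar to participants.

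Under Analysis, the main effect of 'who' is the first comparison listed for Trial 1. The section also states that "we will investigate interaction effects of the different intervention comparisons across the different context areas and population subgroups". Sample size is set for a contrast between two intervention levels inside a single vulnerable subgroup.

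The article gives no reason for the subtitle exception, plans no adjustment for it and does not list it under Limitations.

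**The concern.** A contrast between two messengers can be read as a messenger effect only if other features of the videos do not change with the messenger. In this subgroup one feature, English subtitles, changes exactly with it. If the community representative scores lower or higher than the GP, the data cannot show whether the messenger or the subtitles caused the difference.

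Three planned results are touched: the 'who' contrast inside the subgroup (the kind of contrast the sample size is built on), the 'who'-by-subgroup interaction, and, in diluted form, the pooled 'who' main effect. The Discussion gives the comparison a practical use: if a trusted medical expert does as well as each group's own leader, fewer group-specific productions may be needed. A difference that comes from subtitles could be read as evidence on that question for this community.

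**Working it through.** **Inputs.** From Interventions, Trial 1: subtitle status by messenger, two visual formats, four contexts, videos of up to 2 minutes. From Sample size: 36 per subgroup, 40 recruited, proportions 0.2 and 0.4, correlation 0.61, two-sided alpha 0.05, power 80%. From Participants and setting: six vulnerable subgroups. The documents give no subtitle effect, so its size *s* is an assumption.

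**The plan's own figure.** With the usual McNemar set-up:

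- Both positive: 0.2 x 0.4 + 0.61 x sqrt(0.2 x 0.8 x 0.4 x 0.6) = 0.1995.
- Discordant cells: 0.2 - 0.1995 = 0.0005 and 0.4 - 0.1995 = 0.2005. Their sum is 0.2009 and their difference is 0.20.
- n = [1.96 x sqrt(0.2009) + 0.8416 x sqrt(0.2009 - 0.04)]^2 / 0.04 = 36.98.

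That rounds to 37 against the stated 36. Power at 36 is 78.9%, and 36 / 0.90 = 40. The stated size is reproduced to within rounding and does not depend on the subtitle issue. It matters here only because it fixes a yardstick of 20 points within one subgroup.

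**Aliasing within the subgroup.** The four Trial 1 cells for deaf and hard of hearing participants are:

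| Cell | Who (representative = 1) | Animation = 1 | Subtitles available |
|---|---|---|---|
| GP, talking head | 0 | 0 | 1 |
| GP, animation | 0 | 1 | 1 |
| Representative, talking head | 1 | 0 | 0 |
| Representative, animation | 1 | 1 | 0 |

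Subtitles = 1 - who, so their correlation is -1.0. A design matrix with intercept, who, visual format and subtitles has rank 3 with 4 columns. Adding the who-by-visual interaction gives rank 4 with 5 columns. More participants repeat the same four rows, so the rank does not change. Within each messenger, subtitle status is the same for both visual formats, so the animation versus talking-head contrast is not affected.

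**Where the subtitle effect goes.** Let d be the true 'who' effect (representative minus GP) and s the effect of having subtitles, in percentage points. Assume that subtitles do not differ by messenger in the other five subgroups and that subgroups are equal in size (40 of 6 x 40 = 240, or one sixth).

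- Contrast in this subgroup: d - s.
- Its difference from the average contrast of the other five subgroups: shifted by the full s.
- Pooled 'who' effect: shifted by s x 40/240 = s/6.

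| Assumed size of s | Shift in subgroup contrast | Share of the 20-point target | Shift in pooled contrast |
|---|---|---|---|
| 0 | 0 | 0% | 0 |
| 5 | 5 | 25% | 5/6 = 0.8 |
| 10 | 10 | 50% | 10/6 = 1.7 |

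If subtitles help, the shift favours the GP. If they distract, it favours the representative.

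**The case against.** The strongest reply is that these participants are Auslan users and the plan provides their video content in Auslan. Subtitles are an addition to that, described as available, and nothing in the article shows that this audience needs or uses them. The effect could be zero. This stands as a limit on the size of any bias. It does not remove the confounding, and the plan itself offers subtitles to this subgroup on its other videos.

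It can also be said that the pooled effect hardly moves, that visual format is untouched, and that Trials 2 and 3 contain no GP versus representative contrast. All of this is correct. The planned interaction would reveal a divergent result in this subgroup, but it could not explain it.

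A reader might go further than the text allows in three ways.

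- *That the exception contradicts the Procedure section.* That section says "All information (explanatory statements, survey questions and video information) will be captioned, translated, interpreted or adapted accordingly". The list is joined by 'or', and the section names Auslan as the adaptation for this group, so Auslan without captions satisfies it.
- *That it breaks a promise to keep presentation equal.* The words "will be held as constant as feasible between the intervention levels" refer to scripting, not to presentation, and are qualified by feasibility.
- *That equal subtitles would leave a pure messenger contrast.* They would not. The GP videos would still carry a different, less familiar interpreter. The article requires that separate person only for the GP videos, which suggests, without saying so, that the representative signs directly.

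**Conclusion.** The point holds for one of the six subgroups. Among deaf and hard of hearing participants in Trial 1, subtitle availability is completely aliased with 'who', and no planned analysis can separate them. The subgroup contrast and the 'who'-by-subgroup interaction carry the full subtitle effect. The pooled main effect carries about one sixth of it, given equal subgroup sizes and no subtitle difference by messenger elsewhere.

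A reader might infer that the results are biased toward the GP. The documents do not support that, because they give neither sign nor size for a subtitle effect. The range of 0 to 10 points is an assumption, and zero belongs in it. On that range the subgroup contrast shifts by 0 to 10 points, at most half of the 20-point difference used for sample size, and the pooled contrast by 0 to 1.7 points. The pooled conclusion is therefore little threatened, while the interpretation for this subgroup is. The change is worth making because the confounder is avoidable and cheap to remove.

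**What to change.** Make English subtitles equally available on the GP and community-representative videos shown to the deaf and hard of hearing subgroup, in both visual formats. That is at most 2 formats x 4 contexts = 8 videos of up to 2 minutes, or 16 minutes of footage at most. It needs no extra participants or procedures.

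If production is complete, state the reason for the exception and list it under Limitations. Report the pooled 'who' effect with and without this subgroup, and do not attribute the subgroup's 'who' contrast, or its part in the interaction, to the messenger alone. This costs one extra model run and a few sentences.

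In either case, state when interpreting this subgroup's result that the 'who' contrast includes the different, less familiar interpreter on the GP videos.

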### Sample size

The repeated-measures, latin square design creates an analysis paradigm comparable to a paired-sample comparison of proportions. The least statistical power generated through the helix design arises when there is a simple contrast between two levels of an intervention within a singular vulnerable group category. Power analysis for this context can be approximated by a power analysis conventionally performed for McNemar’s Test, though we will be using linear mixed models for our analyses. A sample size of 36 participants per subgroup will provide 80% to detect a difference in proportions of respondents being “more inclined” or “much more inclined” with a primary outcome statement from 0.2 to 0.4. This assumes a correlation between the outcome proportions of (0.61) and a two-tailed alpha of 0.05. We aim to recruit 40 participants per vulnerable subgroup to allow for ~10% partial completion of the full survey. The study is conducted in a single session so there is no further allowance for loss to follow-up (this is irrelevant in our context). No maximum sample size will be set for the community sample given our online recruitment approach and short time-frame for data collection negating the need to cease the trial “early” due to important findings being identified.

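### In Trial 1's deaf and hard of hearing subgroup, subtitle availability differs exactly with the messenger, so this subgroup's GP-versus-representative contrast cannot be separated from subtitling

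*Protocol article*

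**What the plan says.** Under Interventions, Trial 1, the protocol article sets out a 2x2 factorial: who gives the message (GP or community representative) and the visual format (animation or talking head), spread over four context areas.

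For the deaf and hard of hearing subgroup, Auslan interpretation stays on screen, "with English subtitles also available for all videos except the community representative videos". The same paragraph treats the refugee and asylum seeker subgroup differently: "English subtitles will remain on screen for both community representative and general practitioner videos". For both subgroups, "interpretation of the general practitioner videos will be completed by a different person", who is less familiar to participants than the representative. Participants and setting defines the subgroup concerned as "Deaf and hard of hearing people who are Auslan users".

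The Analysis section lists the messenger main effect as a Trial 1 comparison and adds that "we will investigate interaction effects of the different intervention comparisons across the different context areas and population subgroups". The Sample size section bases its calculation on the least-powered case, which arises "when there is a simple contrast between two levels of an intervention within a singular vulnerable group category". The Limitations section does not mention the subtitle difference.

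**The concern.** The messenger factor has two levels. In this subgroup one level always comes with English subtitles available and the other never does. A difference in stated intention between GP and representative videos could come from the messenger, from the subtitles, or from both, and the data cannot distinguish these.

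The affected estimates are planned ones: this subgroup's own messenger contrast and its comparison with the other subgroups. If subtitles help, the contrast leans towards the GP and can hide a representative advantage. If they distract, it leans the other way. The Discussion names a practical use of the result: if one medical expert works as well as separate community leaders, fewer media items need to be produced. A lean towards the GP would favour that conclusion in this subgroup.

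**Working it through.** **1. What the subtitle effect does to each estimate.** Let the cell means without subtitles be a (GP, talking head), b (GP, animation), c (representative, talking head) and e (representative, animation). Let s be the effect of subtitle availability, taken as equal in the two visual formats. The observed means in this subgroup are a + s, b + s, c and e.

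- Messenger (representative minus GP): (c + e)/2 − (a + b)/2 − s. The whole of s enters.
- Visual format (animation minus talking head): (b + s + e)/2 − (a + s + c)/2 = (b + e)/2 − (a + c)/2. s cancels.
- Messenger-by-visual interaction: (e − c) − [(b + s) − (a + s)] = (e − c) − (b − a). s cancels.

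Over the four cells, messenger (coded as representative) and subtitles correlate at −1.0. A matrix with intercept, messenger, visual, interaction and subtitle columns has rank 4, not 5. With 36 participants and terms for participant and context, the rank is 36 + 3 + 3 = 42 with or without a subtitle column. More recruits or covariates would not change this.

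**2. Reach.** With 36 completers and four ratings each, the subgroup gives 144 ratings: 72 GP, all with subtitles available, and 72 representative, none with them. No messenger-linked subtitle difference is described for the other five subgroups. Trial 2 enrols only the general community and has no representative arm; Trial 3 compares two GP talking-head messages.

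The share of s that enters the pooled messenger effect depends on subgroup sizes:

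- equal subgroups at the recruitment target: 40/240 = 0.167;
- 20 here and 40 in each of the others (assumed): 20/220 = 0.091;
- 40 here and 20 in each of the others (assumed): 40/140 = 0.286.

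**3. The plan's own sample size figure.** Inputs from Sample size: proportions 0.2 and 0.4, n = 36, 80% power; "This assumes a correlation between the outcome proportions of (0.61) and a two-tailed alpha of 0.05".

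- Both positive: p11 = p1p2 + r√(p1q1p2q2) = 0.08 + 0.61 × √(0.16 × 0.24) = 0.1995.
- Discordant total: pd = 0.2 + 0.4 − 2 × 0.1995 = 0.2009 (unrounded); d = 0.20.
- McNemar power: Φ[(d√n − 1.96√pd)/√(pd − d²)] = Φ[(1.200 − 0.879)/0.401] = Φ(0.80) = 0.789.
- Solving for 80% power gives n = 36.98, so 37 against the stated 36. Allowing 10% partial completion, 36/0.9 = 40.

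The stated figure is reproduced closely.

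**4. Hypothetical consequences.** The documents give no subtitle effect. Suppose, purely for illustration, that subtitles raise the GP proportion by 0, 0.05 or 0.10. The single-pair columns use the McNemar formula above. The two-rating columns reflect that the main effect averages two ratings per level. They use a Wald approximation and assume that all four ratings correlate at 0.61:

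Var = (1 + r)/2 × (p1q1 + p2q2) − 2r√(p1q1p2q2), SE = √(Var/36).

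For 0.2 versus 0.4: Var = 0.805 × 0.40 − 1.22 × 0.196 = 0.083; SE = 0.048; 0.20/0.048 − 1.96 = 2.2, so power is about 99%.

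| Assumed rise in GP proportion | Power for a true 0.2 vs 0.4 representative advantage: single pair | Same: two ratings per level | Significant for GP when both messengers are at 0.2: single pair | Same: two ratings per level |
|---|---|---|---|---|
| 0 | 79% | 99% | 2.5% | 2.5% |
| 0.05 | 54% | 87% | 12% | 21% |
| 0.10 | 28% | 52% | 32% | 60% |

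The pooled messenger effect would move by 0.05/6 = 0.008 or 0.10/6 = 0.017 with equal subgroups.

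**The case against.** The strongest reply is that the messenger contrast is a package by design. The protocol presents it as a choice between one GP message usable across groups and a costlier message made for each community. Representatives are invited to co-design messages, scripts are held constant only as far as feasible, and the GP videos have a less familiar interpreter. Subtitling is then one more openly stated component. This has force as an account of the estimand, but the Analysis section labels the effect simply by who gives the message. The interpreter difference is described as part of realising the messenger factor; the subtitle difference is given no reason and is not carried into the other interpreted subgroup.

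It can also be said that Auslan users already receive the message in Auslan, so English text may matter little, and that subtitles being available does not mean they are read. Both points may shrink the effect, but availability still differs exactly with messenger. A representative who signs directly might explain the exception. The document does not say so, and it would not remove the overlap.

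Three stronger readings are tempting. A reader might infer that Trial 1's messenger effect as a whole is compromised. The text supports this for one subgroup only, and the shift in the pooled estimate would be small under the values tried. A reader might take the fall from 79% to 28% as the expected loss of power. It rests on an invented subtitle effect of unknown direction and describes a single-pair contrast, not the main effect with two ratings per level. A reader might also expect equal subtitling to give a clean messenger contrast. It would not, because the interpreter difference is aliased with messenger in the same way.

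**Conclusion.** The point holds, limited to one of six subgroups. In the deaf and hard of hearing subgroup, the messenger contrast and its part of the messenger-by-subgroup interaction cannot be separated from subtitle availability. That follows from the stated design and needs no assumption about size.

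The visual-format effect and the messenger-by-visual interaction are unaffected, given a subtitle effect that is the same in both visual formats; Trials 2 and 3 are unaffected outright. About one sixth of any subtitle effect enters the pooled messenger effect if subgroups are equal, with 0.09 to 0.29 under the unequal sizes assumed above.

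How large a subtitle effect is, and which way it points, cannot be learned from the document, so the power and false-positive figures are illustrations only. This is a worthwhile, inexpensive improvement to a planned subgroup comparison, not a flaw that undermines the trial.

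**What to change.** In Interventions, Trial 1, provide English subtitles on the community representative videos for the deaf and hard of hearing subgroup, matching the arrangement for refugees and asylum seekers. Describe this subgroup's contrast as representative versus interpreted GP, because the interpreter difference remains.

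If subtitles cannot be added, state that this subgroup's contrast combines messenger and subtitling, do not read it as a pure messenger effect, and report the pooled messenger effect with and without this subgroup.

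The cost is a small amount of captioning. The document gives no video count or price; assuming one representative video per context and visual format, 4 × 2 = 8 videos need subtitles. Nothing is re-recorded, and the GP materials shared with Trial 2 stay as they are.
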